## Abstract

**Introduction::**

With dissatisfaction of western medicine, traditional Chinese medicine becomes alternative treatment for idiopathic pulmonary fibrosis patients. The common syndrome of idiopathic pulmonary fibrosis (IPF) is qi and yin deficiency syndrome. The prescription, Modified Maimendong Decoction (MMD), is usually used for IPF patients with qi and yin deficiency syndrome. However, there is no convinced evidence for the efficacy and safety of MMD to treat IPF.

**Methods::**

A double-blind, placebo-controlled, randomized clinical trial was put forward by us. After a 1-day run-in period, 60 eligible patients will be included in the study. These subjects will be allocated to the experiment group or control group in a 1:1 ratio. Patients in the experiment group will take MMD plus Pirfenidone capsule. At the same time, patients in the control group will receive a matched placebo plus Pirfenidone capsule. All subjects will receive 24 weeks of treatment and follow-up period. The primary outcomes are the mean change from the baseline in forced vital capacity and times of acute exacerbations at week 4, 12, 24. Secondary outcomes are the mean change from baseline in the St. George's respiratory questionnaire total score, forced expiratory volume in 1 second percentage/forced vital capacity, diffusing capacity of Carbon monoxide, brain natriuretic peptide, and curative effect of traditional Chinese medicine syndrome at week 4, 12, and 24. Any side effects of the treatment will be recorded.

**Discussion::**

The results of this trial will provide the evidence for the effect of MMD in patients with idiopathic pulmonary fibrosis.

## Introduction

1

Idiopathic pulmonary fibrosis (IPF) is a disease characterized by diffuse alveolitis and alveolar structural disorders that eventually lead to pulmonary fibrosis. The pathological and radiological manifestations of idiopathic pulmonary fibrosis are usual interstitial pneumonia. The main clinical manifestations are unexplained chronic dyspnea, cough, bursting sound at the base of both lungs and/or clubbing fingers. The prognosis of idiopathic pulmonary fibrosis is poor, and the median survival time after diagnosis is only 3 to 5 years.^[1]^ In the course of the disease, it can lead to many complications such as emphysema, pulmonary hypertension, lung cancer, venous thromboembolism.^[2]^ In the progression of the disease, it may eventually develop into respiratory failure and die. Epidemiological investigation found that the incidence of IPF is 2 to 29/100,000.^[3,4]^ The results of a systematic review showed that the incidence of IPF was 2.8 to 9.3/100,000, and 3 to 9/100,000 in North America and Europe, which was higher than that in South America and Asia (<4/100,000).^[5]^ With the development of medical technology, the diagnosis rate and incidence of IPF are increasing year by year, which not only brings serious health problems to patients, but also brings heavy economic burden to the society.^[6]^ At present, there is no specific drug for the treatment of IPF in western medicine. In 2016, Chinese experts agreed on the diagnosis and treatment of idiopathic pulmonary fibrosis^[7]^ to recommend antacid drugs such as Pyrifenidone and Nidanib to treatment, but it is difficult to control the occurrence and development of IPF. Therefore, to further find a solution for the prevention and treatment of IPF, reduce the medical cost and reduce the social burden has become an important task for the prevention and treatment of the disease.

Traditional Chinese medicine (TCM) has the characteristics of multi-targets in the treatment of IPF and plays an important role in the adjuvant treatment of IPF. IPF belongs to the disease name of western medicine, and there is no corresponding disease name in the ancient books of TCM. At present, the disease can be classified as “lung arthralgia (a disease of the lung due to external pathogen blocking lung qi, marked by dyspnea and vomiting, chest and back pain)” and “lung withered (a disease of the lung due to chronic cough, marked by atrophy of the lung with shortness of breath and expectoration)” in TCM according to the clinical symptoms, etiology and pathogenesis of IPF. The pathogenesis of “pulmonary arthralgia” is consistent with IPF in western medicine. In the process of IPF, the capillaries in the lung proliferate and dilate, the wall thickens, a large number of fibrous connective tissue proliferates and the blood vessels contract, and the number of capillaries decreases or even atresia.^[8]^

Using Chinese medicine in conjunction with Western medicine showed greater efficacy than using the Western medicine alone in delaying the decline of pulmonary function and quality of life with good safety. A large number of experiments have confirmed that TCM prescription is effective in the auxiliary treatment of IPF. Ren Luyao et al^[9]^ used Yiqi Huoxue Guben recipe combined with acetylcysteine granule to treat idiopathic pulmonary fibrosis. The results showed that Yiqi Huoxue Guben recipe could delay the decline of lung function, improve respiratory symptoms, increase activity endurance and improve the quality of life. It is effective in the clinical treatment of idiopathic pulmonary fibrosis. Yan Jingjing et al,^[10]^ who treated idiopathic pulmonary fibrosis with Qingfei Huaxian decoction combined with western medicine, concluded that Qingfei Huaxian decoction in patients with IPF can effectively reduce clinical symptoms, improve pulmonary function, reduce the level of pulmonary fibrosis indexes (serum laminin, hyaluronic acid), and has high safety. Xue Honghao et al^[11]^ did a Clinical study which has shown that chemical fiber decoction can reduce Borg dyspnea score and St. George's respiratory questionnaire quality of life score in patients with idiopathic fibrosis, as well as serum TNF-α and TGF-β levels. It is concluded that chemical fiber decoction may play a therapeutic role in patients with IPF by inhibiting inflammatory reaction. Yuan Jie's Clinical trial results show that Xuefu Zhuyu decoction combined with N-acetylcysteine has a good effect on inhibiting the progression of idiopathic pulmonary fibrosis, can effectively alleviate inflammatory reaction, improve lung function, and has high safety.^[12]^ Duan Chenxia et al^[13]^ found that Peiyuan Quyu recipe has a significant effect on improving the clinical symptoms of IPF of phlegm and blood stasis, but also can improve the index of pulmonary function, reduce the acute aggravation of the disease, significantly improve the exercise endurance and quality of life, and the curative effect is reliable. Zhang Wei et al^[14]^ by using Qingjin Yifei decoction to treat rats with idiopathic pulmonary fibrosis of phlegm-heat accumulation in the lung, they found that Qingjin Yifei decoction could reduce the expression of VEGFmRNA and PDGF, thus reduce capillary permeability, dilate pulmonary arteries and veins, and improve vascular remodeling. Through clinical observation and animal experiments, Zhang Guicai et al^[15]^ found that Huqi Huoxue decoction can reduce the deposition of collagen in the lungs and improve the symptoms of patients with idiopathic pulmonary fibrosis by inhibiting the expression of TGF- β and its protein. MengLi^[16]^ found that Yangqing Kangxian recipe has a good protective and long-term effect on pulmonary fibrosis by anti-inflammation and reducing fibrosis.

Maimendong decoction comes from *the Synopsis of the Golden Chamber* (JinGui YaoLue) written by Zhang Zhongjing in the Han Dynasty. The prescription is composed of Radix Ophiopogonis japonica (Maimendong), Pinellia ternate (Banxia), Radix Ginseng (Renshen), Licorice (Gancao), Japonica rice (Jingmi), Jujube (Dazao). Chinese researchers have done a large number of experiments to confirm the efficacy of Maimendong decoction in the treatment of idiopathic pulmonary fibrosis. A rat experimental study found that Radix Ophiopogonis japonica can reduce the degree of pulmonary fibrosis in rats with IPF, probably by increasing the level of BMP-4.^[17]^ Liu Xiaoming et al^[18]^ showed that Pinellia ternata had the same effect as pirfenidone in improving Nrf2 antioxidant index and regulating antioxidant gene expression. Pinellia ternata can interfere with pulmonary fibrosis by interfering with the mechanism of oxidation-antioxidation. Some studies have shown that ginsenoside 1 (Rg1), the main active component of Panax ginseng, has a protective effect on bleomycin-induced pulmonary fibrosis in rats, and its mechanism may be related to down-regulation of transforming growth factor β-1 and upregulation of Cav-1.^[19]^ Some experiments have found that compound glycyrrhizin, an effective component of licorice, can reduce pulmonary fibrosis in rats with IPF, and its mechanism may be related to regulating the level of free radicals and reducing the oxidative damage of free radicals to lung tissue structure.^[20]^ These experiments provide a pharmacological basis for Maimendong decoction in the treatment of IPF. The use of Modified Maimendong Decoction (MMD) in TCM has accumulated a great deal of clinical experience in the adjuvant treatment of IPF. Bai Wenmei^[21]^ concluded that the treatment of IPF patients with Maimendong decoction combined with pirfenidone can significantly relieve clinical symptoms, improve lung function and quality of life, and effectively delay pulmonary fibrosis by a clinical trial. The clinical trial of Yu long^[22]^ showed that Jiawei Maimendong decoction combined with conventional western medicine can reduce the symptoms and improve lung function of patients with IPF. A literature review shows that^[23]^ Maimendong decoction is effective in the treatment of pulmonary fibrosis, but its mechanism and safety of clinical application need to be further explored. These clinical studies have confirmed that MMD can treat IPF, but the quality of the literature is generally low. There is still a lack of high-quality evidence-based medicine to confirm the clinical efficacy and safety of MMD in the treatment of IPF. Therefore, we designed this randomized controlled trial to evaluate the clinical efficacy and safety of MMD in adjuvant treatment of IPF.

## Methods

2

### Study design

2.1

An independent committee, including clinicians of respiratory department, statisticians and ethics experts, will be set up to perform the study design. A randomized, prospective, double-blind placebo-controlled clinical trial will be carried out to evaluate the efficacy and safety of MMD. This trial has been registered with the Chinese Clinical Trial Registry (no ChiCTR2000036021, registered on August 21th, 2020). This study will act in accordance with the Standard Protocol Items: Recommendations for Interventional Trials 2013 statement (see Fig. 1). Figure 2 shows a flowchart of the study.

**Figure 1 F1:**
[figure not shown]
SPIRIT figure of enrollment, interventions, and assessments.^[1]^ Laboratory tests: blood, urine, feces, electrocardiogram, and kidney and liver function tests. BNP = brain natriuretic peptide, DL_CO_ = diffusing capacity of Carbon monoxide, FEV1 = forced expiratory volume in 1 second percentage, FVC = forced vital capacity, MMD = modified Maimendong decoction, SGRQ = St. George's respiratory questionnaire, SPIRIT = standard protocol items recommendations for interventional trials, TCM = traditional Chinese medicine.

**Figure 2 F2:**
[figure not shown]
Flow chart of the study design.

### Ethics approval and consent to participate

2.2

The study protocol will has been approved by the China Ethics Committee of Registering Clinical Trials in September 2020 and has been registered on the Chinese Clinical Trial Registry (http://www.chictr.org.cn/showprojen.aspx?proj=59112) with number ChiCTR2000036021 on August 21th, 2020. This trial will follow the principles of the Declaration of Helsinki and the International Ethical Guidelines for Biomedical Research Involving Human Subjects. Only when subjects provide informed consent, can they take part in this study.

### Study population and recruitment

2.3

IPF patients will be recruited by respiratory physicians from respiratory clinics at the Hospital of Chengdu University of Traditional Chinese Medicine (Chengdu, China), a national clinical trial and research center of TCM. Subjects will be recruited via all kinds of method like advertisement and doctor referrals. All patients have to get the advice by a specialist in Department of Respiratory Medicine before receiving treatment. All the patients will sign the informed consent before enrollment. Recruitment will last for a year from September 2020 or until the total sample are completed.

### Sample size calculation

2.4

Calculation of the sample size was based on the primary outcome variable, forced vital capacity (FVC). According to previous study,^[20]^ the mean of FVC in control group was 3.07 L and the standard deviation was 0.71 L after taking Pifenidone. With oral MMD plus Pifenidone, the mean in experiment group was 3.81 L, and the standard deviation was 0.85 L. We employed following formula to calculate the sample size in each group: n *= (μ*_*α*_* + μ*_*β*_*)*^*2*^ *×* *(1+1/k)* *×* *σ*^*2*^*/ (μ*_*2*_*-μ*_*1*_*)*^*2*^, where *σ*^2^ is overall variance, which was estimated as sample variance *s*^2^ just like the formula *s*^*2*^*= (s*_*1*_^*2*^* + ks*_*2*_^*2*^*) / (1 + k)*. The proportion of subjects between the experiment and control groups was set to 1:1 (k = 1). The study was designed to have a power of approximately 90% and 1-side level of significance of 0.05 (a = 0.05, β = 0.1). *μ*_2_, *μ*_1_, *s*_1_, and *s*_2_ are mean and standard deviations in the control and experiment groups respectively. Twenty-three patients are needed in each group based on the formula mentioned above. Considering a 10% of drop-out rate, approximately 26 patients should initially be recruited in each group. In the study, 30 subjects will be recruited in each group actually, with a total of 60 subjects.

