### Outcomes measure

3.2

The following outcomes for the subjects will be assessed by independent researchers who do not know the allocation.

Primary outcomes: The primary outcomes are the change from the baseline in FVC at week 4, 12, 24 and times of acute exacerbations at week 4, 12, 24.

Secondary outcomes:

1.The change from baseline in the St. George's respiratory questionnaire total score at week 4, 12, and 24.2.The change from baseline in forced expiratory volume in 1 second percentage/FVC at week 4, 12, and 24.3.The change from baseline in diffusing capacity of Carbon monoxide at week 4, 12, and 24.4.The change from baseline in brain natriuretic peptide at week 4, 12, and 24.5.The change from baseline in curative effect of TCM syndrome at week 4, 12, and 24.

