## Discussion

4

There are 2 different theories in TCM and Western medicine about recognition and treatment of diseases. Diagnosis of TCM will combine disease, syndrome, relevant clinical signs and symptoms, with all together to establish a treatment principle. Syndrome differentiation is the core of TCM practice, and we formulate the MMD to treat IPF patients for this study with qi and yin deficiency syndrome.

IPF is a serious global health problem with poor prognosis. Available medications for IPF cannot get the satisfactory results for patients at present. There have been many years of TCM prescription used in adjuvant treatment for IPF in China. MMD is a common formula for the disease.

As we know, this is the first double-blind, placebo-controlled, randomized clinical trial to evaluate the efficacy and safety of MMD plus western medicine in the treatment of IPF. This study will provide a preliminary evaluation of the efficacy and safety of MMD in IPF. Sixty subjects will be recruited in this clinical study. At the same time, they will be divided into 2 groups according to the randomization performed before recruitment. However, there are some limitations in the study. On the one hand, the sample size is too small, which calculated based on previous research, and it may be smaller than it needs. On the other hand, a follow-up period of 24 weeks may be relatively short duration to assess the efficacy and safety of TCM in IPF, a chronic disease.

In conclusion, this study hypothesis that MMD plus Pirfenidone can improve pulmonary function, decrease the time of acute exacerbations and improve quality of life with IPF patients. If the results of the study are positive, it will be possible to give another option in the area of adjuvant treatment with IPF.

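### The stated power of about 90% is calculated on post-treatment FVC levels, while the primary outcome is change from baseline, and the cited source is elsewhere described as a rat experiment; the power for the primary endpoint is therefore not established

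*Protocol article*

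**What the plan says.** Section 2.4 (Sample size calculation) says that the calculation rests on the primary outcome variable, FVC, and credits its inputs to reference 20. For pirfenidone alone, "the mean of FVC in control group was 3.07 L and the standard deviation was 0.71 L after taking Pifenidone". For pirfenidone plus the decoction, "the mean in experiment group was 3.81 L, and the standard deviation was 0.85 L". The design has a "power of approximately 90% and 1-side level of significance of 0.05". The result is 23 patients per group, 26 after a 10% allowance for drop-out, and 30 actually planned.

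Section 3.2 (Outcomes measure) defines the FVC outcome differently: "The primary outcomes are the change from the baseline in FVC at week 4, 12, 24". The abstract agrees with section 3.2.

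The Introduction uses reference 20 for an experiment in which "compound glycyrrhizin, an effective component of licorice, can reduce pulmonary fibrosis in rats with IPF". It uses reference 21 for a clinical trial of Maimendong decoction combined with pirfenidone.

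The Discussion lists as a limitation that "the sample size is too small, which calculated based on previous research, and it may be smaller than it needs".

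**The concern.** A power statement belongs to one variable, one assumed difference and one SD. Here the difference (0.74 L) is a gap between two groups' FVC after treatment, and the SDs (0.71 and 0.85 L) measure how much patients differ from one another. The trial will compare changes within patients. For that it needs the expected difference in mean change and the SD of change, and the article gives neither. It also gives no baseline FVC for the earlier study, so a reader cannot tell how much of the 0.74 L was there before treatment.

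The source cannot be traced either. A rat experiment cannot supply human FVC on pirfenidone with and without the decoction, so section 2.4 and the Introduction cannot both be right about reference 20.

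At stake is how the result is read. If the trial shows no significant difference, the 90% figure invites the conclusion that a worthwhile effect has been ruled out. The plan does not support that reading for FVC change.

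**Working it through.** **Inputs from section 2.4.** Means 3.07 and 3.81 L; SDs 0.71 and 0.85 L; ratio 1:1; power 90%; level 0.05, stated as one-sided. Section 3.6 (Statistical analysis) tests at two-sided 0.05.

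**Reproducing the plan's figure.**
- Pooled variance = (0.71² + 0.85²)/2 = 0.6133, so SD = 0.783 L.
- Difference = 3.81 − 3.07 = 0.74 L; standardised difference = 0.74/0.783 = 0.945.
- n per group = 2 × (z_α + z_β)² × 0.6133/0.74².
- Two-sided 0.05: 2 × (1.960 + 1.282)² × 0.6133/0.5476 = 23.5, rounded up to 24. At n = 23 the power is 89.3%.
- One-sided 0.05: 2 × (1.645 + 1.282)² × 0.6133/0.5476 = 19.2, rounded up to 20.
- Drop-out: 23/0.90 = 25.6, so 26.

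The stated 23 thus agrees, to within one patient, with a two-sided calculation on FVC levels. The one-sided label is a separate inconsistency; two-sided 0.05 is used from here on.

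**Moving to change from baseline.** With equal SDs at both visits and correlation r between them, SD of change = 0.783 × √(2(1 − r)). The documents do not give r, so these values are assumptions:

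| r (assumed) | SD of change |
|---|---|
| 0.5 | 0.783 L |
| 0.8 | 0.495 L |
| 0.9 | 0.350 L |
| 0.95 | 0.248 L |

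**Case A: 0.74 L is the true difference in change.** With 27 per arm (30 less 10%), power is about 93% at r = 0.5 and above 99% at r = 0.8 or more.

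**Case B: the true difference in change is smaller.** The differences and SDs below are assumptions; the documents give none. Two-sample t-test, 27 per arm:

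| True difference | SD of change 0.3 L | SD of change 0.5 L |
|---|---|---|
| 0.2 L | 67% | 30% |
| 0.3 L | 95% | 58% |

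**What the planned size can detect** (two-sided 0.05, t-test), in units of the SD of change:

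| Patients per arm | 80% power | 90% power |
|---|---|---|
| 27 | 0.78 SD | 0.90 SD |
| 30 | 0.74 SD | 0.85 SD |

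For an SD of change of 0.25 to 0.50 L, 90% power with 27 per arm needs 0.90 × 0.25 = 0.22 L to 0.90 × 0.50 = 0.45 L.

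**The case against.** The strongest reply is that planning on levels is usually the cautious choice. In a randomised comparison the expected baselines are equal, so the expected difference in level equals the expected difference in change. When visits correlate above 0.5, change has the smaller SD. On that view 23 per group is more than enough. This stands as far as it goes, and it rules out saying that the mismatch by itself lowers power. It depends, however, on 0.74 L being a real treatment difference, and that is the input with no traceable source and no baseline to check it against.

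A reader might infer that the trial is underpowered, or that 0.74 L is implausible for a treatment meant only to slow decline. The documents support neither. The low powers in Case B come from replacing 0.74 L with smaller differences that the article does not give. Delaying decline is the Introduction's remark about Chinese medicine in general; the Discussion's own hypothesis is improved pulmonary function. That the 0.74 L contains baseline imbalance is a possibility, not something shown.

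A reader might also take reference 21 to be the intended source. It may be, and the marker may be a numbering slip, but the article does not confirm it, and the decoction described there has a different ingredient list from the modified formula in section 2.9.

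Two further points are fair. The Discussion already admits that the sample may be too small and calls the trial a preliminary evaluation, which softens the risk of misreading but leaves the 90% claim in place. Section 3.6 carries the last value forward under intention to treat, so the analysis aims at 30 per arm; both sizes are therefore shown for the detectable difference.

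**Conclusion.** The concern holds in this form: the power of about 90% describes post-treatment FVC levels and is not established for change from baseline in FVC, and the cited source contradicts the Introduction. Both points can be read directly from the article and need no assumption.

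The size and direction of the error cannot be fixed from the documents. Power is above 90% if 0.74 L is the true difference in change and visits correlate above 0.5. It is 30 to 67% if the true difference is 0.2 L, and 58 to 95% if it is 0.3 L, with an assumed SD of change of 0.3 to 0.5 L and 27 per arm. What can be said firmly is that 27 to 30 patients per arm give 90% power for a difference of 0.90 to 0.85 SD of change.

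**What to change.** Keep 60 patients.

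1. In section 2.4, replace the 90% claim with the difference in FVC change that the planned size can detect at the two-sided 0.05 level of section 3.6: 0.78 SD of change (80% power) and 0.90 SD (90% power) with 27 per arm, or 0.74 and 0.85 SD with 30 per arm. Convert to litres over a stated range for the SD of change, labelled as an assumption unless a source for it is given. For example, 0.25 to 0.50 L gives about 0.22 to 0.45 L at 90% power with 27 per arm.
2. Name the clinical study that supplied the 3.07 and 3.81 L, and reconcile the use of reference 20 in section 2.4 with its use in the Introduction. If that study reports baseline values or change data, quote them.
3. Say that a non-significant FVC result will be interpreted from its confidence interval.

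The cost is a short recalculation and some protocol wording. No patients, visits or analyses are added.

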### Statistical analysis

3.6

The data will be analyzed by the SPSS V.23.0 (Chicago, IL) software package after the collection of data from the entire sample. All the *P*-values will be for 2-sided distributions, with a significant level of .05 for α. A descriptive analysis of the baseline date of the sample will be performed. All the quantitative variables will be analyzed by the Kolmogorov-Smirnov test with Lilliefors corrections, to ascertain whether the variables follow a normal distribution or not. The initial homogeneity between the groups will be also analyzed (ANOVA or Kruskal–Wallis depending of the normality of data distribution).

The measurement data will be examined using group *t*-tests or non-parametric tests, the count data will be tested using a Chi-square test or Fisher exact probability method, and the grade data will be tested using nonparametric tests.

All data analyses will be conducted with the intention to treat principles. If there are losses of follow-up, the outcome variables that have not been recorded will be completed with the last data recorded for each subject of these data.

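### The sample size section states a one-sided 0.05 level while the analysis is two-sided, and its 23 per group does not follow from the printed formula at the stated level

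*Protocol article*

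**What the plan says.** Section 2.4 (Sample size calculation) bases the size on FVC. It takes from an earlier study that "the mean of FVC in control group was 3.07 L and the standard deviation was 0.71 L" on pirfenidone and that, with MMD added, "the mean in experiment group was 3.81 L, and the standard deviation was 0.85 L". It prints a normal-approximation formula for two means with a pooled variance and allocation ratio k = 1. The error rates are given as "a power of approximately 90% and 1-side level of significance of 0.05". The result is reported as: "Twenty-three patients are needed in each group based on the formula mentioned above". A 10% drop-out allowance raises this to 26 per group, and the section then sets recruitment at 30 per group, 60 in all.

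Section 3.6 (Statistical analysis) states that all P-values "will be for 2-sided distributions, with a significant level of .05 for α". It makes no exception for FVC.

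**The concern.** Two things do not fit together. First, the level used for planning (one-sided 0.05) is not the level used for testing (two-sided 0.05). A one-sided 0.05 test corresponds to a two-sided test at 0.10, so the planning statement describes a more lenient test than the one that will be run. Second, section 2.4 prints the formula and every input, so its result can be checked, and at the stated one-sided level the formula does not return 23.

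What is at stake is the credibility of a figure on which the trial's size rests. A reader who checks section 2.4 gets a different number and cannot tell from the text whether the label, the arithmetic or the planned test is wrong.

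**Working it through.** **Inputs, all from section 2.4 except the last**

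- Control FVC: mean 3.07 L, SD 0.71 L
- Experiment FVC: mean 3.81 L, SD 0.85 L
- Difference: 3.81 − 3.07 = 0.74 L; squared, 0.5476
- Allocation: k = 1
- Power: 90% (beta = 0.1), normal quantile 1.282
- Level: one-sided 0.05 in section 2.4, quantile 1.645; two-sided 0.05 in section 3.6, quantile 1.960

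**Pooled variance**, by the article's expression with k = 1:

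s² = (0.71² + 0.85²) / 2 = (0.5041 + 0.7225) / 2 = 0.6133, so s = 0.783 L.

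**Formula as printed**: n per group = (z for alpha + z for beta)² × (1 + 1/k) × s² / (difference)².

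**Attempt to reproduce 23 at the stated one-sided level**

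n = (1.645 + 1.282)² × 2 × 0.6133 / 0.5476 = 19.18, so 20 per group. The stated 23 is not reproduced.

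**Same formula at the two-sided level of section 3.6**

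n = (1.960 + 1.282)² × 2 × 0.6133 / 0.5476 = 23.54, so 24 per group. Rounded down, this is 23.

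**Power at 23 per group on the same inputs**

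| Level | Normal approximation | t-test (noncentral t) |
|---|---|---|
| One-sided 0.05 | 94.1% | 93.4% |
| Two-sided 0.05 | 89.3% | 88.0% |

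The stated power of approximately 90% fits the two-sided row better than the one-sided row.

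**Drop-out step**

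- As stated: 23 / 0.9 = 25.6, so 26. This step reproduces.
- Corrected: 24 / 0.9 = 26.7, so 27 per group, 54 in total.

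**Planned enrolment**

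With 30 per group and 10% drop-out, 30 × 0.9 = 27 remain evaluable. Two-sided t-test power on the article's inputs is then 92.6%; with all 30 it is 94.9%.

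**The case against.** The best defence is that this is a single wrong label plus a rounding choice. At two-sided 0.05 the formula gives 23.54. The article claims only approximate 90% power, and 23 per group delivers 89.3% by its own method. The drop-out step is correct, and 30 per group exceeds the corrected need. All of this stands, and it limits the point to a reporting correction. It does not remove it: the text still gives a one-sided level, that level yields 20, and a required sample size is rounded up.

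Three stronger readings are tempting and should not be drawn.

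- *That the error rate of the trial's test is ambiguous.* A reader might infer that a two-sided P-value between .05 and .10 could be called significant by appeal to section 2.4. But section 2.4 concerns planning. Section 3.6 is the only place that sets a decision rule, and it is explicitly two-sided and the stricter of the two.
- *That the trial is underpowered because of this.* On the article's own assumptions it is not, since 27 per group are needed after drop-out and 30 are planned. Section 4 concedes that the sample may be too small, but that does not follow from this discrepancy.
- *That 23 has no recoverable origin.* Rounding down the two-sided result explains it most simply. Other routes are conjecture and conflict with the text. Using only the larger SD at the one-sided level gives 22.6, but the article prints a pooled variance. Inflating 20 for drop-out gives 20 / 0.9 = 22.2, so 23, but the article applies drop-out after reaching 23.

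**Conclusion.** The point holds as an internal inconsistency of minor to moderate severity. Sections 2.4 and 3.6 state different sidedness, and 23 per group is not what the printed formula gives at the stated one-sided level (19.2, so 20). At two-sided 0.05 the formula gives 24, one more than stated, and 27 per group after drop-out, one more than the stated 26. Enrolment of 30 per group is not affected, and type I error is not inflated under section 3.6.

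That the label rather than the number is the slip is an inference from the near match of 23.54 and 23; the article does not say so. All power figures here take the assumed FVC means and SDs as given. Those inputs are FVC levels on treatment, whereas section 3.2 defines the primary FVC outcome as change from baseline. Correcting the significance level does not show that the inputs suit that outcome.

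**What to change.** In section 2.4:

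1. Replace the one-sided level with a two-sided significance level of 0.05, to agree with section 3.6.
2. Write the formula's first quantile for alpha/2 instead of alpha. Changing the words alone would leave the notation at odds with a two-sided level.
3. Restate the requirement as 24 per group, and 27 per group after 10% drop-out (24 / 0.9 = 26.7), keeping to the normal-approximation formula throughout.
4. Leave recruitment at 30 per group. If a power is quoted for that enrolment (about 93% by t-test with 27 evaluable per group), name the method and say that it is conditional on the assumed FVC means and SDs.

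The cost is a text correction. Design, enrolment and the analysis in section 3.6 stay as they are.
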